#### Routine Standard Care Group/Control Group

In this group, the children will undergo visual acuity testing and refraction by an optometrist. The pediatric ophthalmologist will perform detailed ocular examination and advise necessary investigations to diagnose and formulate a treatment plan. Basic counseling will be done by the consultant regarding the ocular condition, treatment, and need for follow-up. No additional counseling or reminders will be performed for these patients. They will be discharged from the department and advised for follow-up as per the hospital protocol. The follow-up schedule as per the hospital protocol for common ocular conditions is shown in Table 1.

**Table 1 table1:** Schedule for follow-up for different ocular conditions.

Ocular condition	Recommended guidelines for follow-up [11]
Congenital naso-lacrimal duct obstruction	Once every 4 weeks
Keratitis	Depending on severity, at least once a week
Allergic conjunctivitis	Once every 2 weeks
Ocular injury	Depends on severity of injury, daily to once a week
Pediatric cataract	Once every 2 weeks
Strabismus	Once every 2 weeks
Amblyopia	Once every 4 weeks
Retinopathy of prematurity	Once every 2 weeks

### Outcomes

The primary outcome is the proportion of children completing all 3 follow-up visits in the routine standard care group, counseling group, and reminders through SMS texts and phone call group.

The secondary outcomes include the effect of parental or guardian education status in compliance to follow-up, the visual status of the children in subsequent follow-up visits, the effect of traveling distance and cost in compliance to follow-up, and the cost-effectiveness of the intervention.

### Independent Variables

The independent variables will include the following sociodemographic factors: gender, age, ethnicity, educational status, occupation of parent or guardian, attendant relationship with the child (of parent or guardian attending with the child), distance traveled, and cost for the travel to the hospital.

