## Introduction

Childhood visual impairment and blindness remains an important public health issue. It is estimated that around 14 million children in the world are blind [1]. The Nepal Pediatric Ocular Disease study found that the prevalence of blindness and visual impairment in the community was 0.068% (95% CI 0.02-0.12) and 0.097% (95% CI 0.04-0.15), respectively [2]. Increasing the global knowledge base for planning for childhood eye care services is a top priority in order for children with visual impairment to realize their full visual potential [3]. Follow-up of pediatric patients is important for their regular ocular morbidity monitoring, especially for amblyopia management [4]. Bharatpur Eye Hospital (BEH) observed that there was poor adherence to follow-up visits. An exploratory observation of data of the first week (January 1, 2010, to January 7, 2019) revealed that the follow-up compliance was very low among children aged 0 to 16 years in the pediatric department. Among the children advised for follow-up, only 22% were found to have come for at least 1 follow-up visit. A problem analysis showed that a lack of awareness in children and their parents regarding the importance of follow-up and patients forgetting dates of the follow-up visit (usually when there is long gap for follow-up) may be the major contributing factors for poor adherence to follow-up.

A study from India revealed that distance and cost were major barriers, as was the inability of the eye care center to communicate the importance of follow-up [5]. Another study done in Nepal found poor follow-up rates for patients following cataract surgery, which, however, improved after implementation of a high-quality pediatric counseling service, follow-up program, tracking system, and cell phone reminders [6]. Many studies have compared different methods of reminder options like telephone calls, email, and SMS text messaging in order to improve the compliance to follow-up [7-10]. Hence, a public health intervention study has been planned to estimate the effect of intervention package (counseling and reminder SMS texts and phone calls) for improving the follow-up rates in pediatric patients.

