#### Multivariate Analysis

Multivariate logistic regression analysis will be performed to adjust for the simultaneous effects of multiple factors on the outcome variable. The criteria for inclusion of factors in the multivariate analysis are to include all variables from the univariate analysis with a *P* value of .1 along with all the variables of known importance. To assess the importance of each variable included in the model, the Wald statistic for each variable will be used.

Before the multivariate analysis is conducted, the association among independent variables will be checked by a chi-square test. For independent variables having more than 2 categories, dummy variables will be created. All the variables meeting the above selection criteria will be entered one by one, starting with the highly significant factors from the univariate analysis. The overall significance of independent variables in the model will be assessed by likelihood ratio test (G statistic). Selection of the final model will be based on parsimony, biological interpretability, and statistical significance. The parameters of the logistic regression model will be estimated by the maximum likelihood method. The adjusted ORs and their 95% CIs will be computed using the estimates of parameters of the final model. The dependent variable will be dichotomous: either compliance with the follow-up instruction has increased, or it has remained changed (no difference) from before the intervention study to after it. The final model will be tested for goodness of fit by Hosmer- Lemeshow chi-square (*Χ*^2^) statistic. *P* values will be noted to assess the model fit. Imputation and intention to treat analysis will also be conducted (if required).

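### The adjusted model is built by P-value selection and never states that study group is always kept, so the adjusted group effects can be dropped or exaggerated

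*Protocol article*

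**What the plan says.** The primary objectives (end of the Introduction) ask whether counseling and whether reminders raise follow-up. The Outcomes section defines the primary outcome as the proportion completing all 3 visits in each of the three groups, and Compliance to Follow-up states the purpose as a comparison between them.

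The modelling text is built differently. Independent Variables reads "The independent variables will include the following sociodemographic factors: gender, age, ethnicity, educational status, occupation of parent or guardian", then adds the attendant's relationship to the child, "distance traveled, and cost for the travel to the hospital". Study group, ocular condition and visit interval are not listed.

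Multivariate Analysis then fixes a selection rule:
- Entry: "include all variables from the univariate analysis with a *P* value of .1 along with all the variables of known importance".
- Order: "All the variables meeting the above selection criteria will be entered one by one, starting with the highly significant factors from the univariate analysis".
- Coding: "For independent variables having more than 2 categories, dummy variables will be created".
- Final model: "Selection of the final model will be based on parsimony, biological interpretability, and statistical significance".

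On visit gaps, the Introduction lists among the possible major contributors to poor adherence "patients forgetting dates of the follow-up visit (usually when there is long gap for follow-up". Table 1 sets intervals by ocular condition, from daily or weekly up to every 4 weeks.

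**The concern.** This rule suits a search for risk factors. In a trial that compares interventions, the group effect should be estimated whatever its P value. Followed as written, the rule could take group, or one of its two indicators, out of the adjusted model because it was not significant.

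Three things follow. A group effect reported only when it passes a significance screen is, on average, too large. Its confidence interval takes no account of the selection. An effect that fails the screen has no adjusted estimate at all.

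Ocular condition, or the visit interval that goes with it, has no assured place in the model either. The protocol itself links forgetting to long gaps, and reminders act on forgetting. Allocation is a fixed rotation without stratification by condition (Study Procedure), so imbalance between groups in condition is not controlled by design.

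**Working it through.** **Inputs.** The hypothesised rates are 22% for control, 50% for counseling and 25% for reminders (Introduction). The total is 264, or 264/3 = 88 per group, with 10% loss (Sample Size), which leaves 88 × 0.9 ≈ 79 per group. The screening level is .1 (Multivariate Analysis). The 22% is the hospital's rate for at least 1 follow-up visit. It is used here as the baseline because the protocol's own hypothesis uses it.

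**The plan's own figure.** For 50% v 25%, two-sided alpha 0.05/3 = 0.0167 and 80% power, with pooled variance under the null:

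n = [z(1−α/2)·√(2p̄(1−p̄)) + z(0.80)·√(p1q1+p2q2)]² / (p1−p2)²

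= [2.394 × √0.46875 + 0.842 × √0.4375]² / 0.0625 ≈ 77.1, so 78 per group.

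With 10% loss, 78/0.9 = 86.7, so 87 per group and 261 in total. The stated 264 is reproduced to within 3.

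**Reading 1: each group dummy is screened singly.** Take reminder versus control at 88 per group.
- p̄ = (0.22 + 0.25)/2 = 0.235, and SE = √(2 × 0.235 × 0.765/88) = 0.0639.
- The true difference is 0.03/0.0639 = 0.469 standard errors. P < .1 needs 1.645.
- P(pass in the right direction) = 1 − Φ(1.645 − 0.469) = 1 − Φ(1.176) ≈ 0.120.
- P(pass in the wrong direction) = Φ(−1.645 − 0.469) = Φ(−2.114) ≈ 0.017.
- P(pass) ≈ 0.137, so the contrast fails in about 86% of trials. Of those that pass, 0.017/0.137, or about 13%, have the wrong sign.
- To pass, the observed difference must be at least 1.645 × 0.0639 ≈ 10.5 points, against a true 3 points.
- The true odds ratio is (0.25 × 0.78)/(0.75 × 0.22) = 1.18. In simulation, the median odds ratio among contrasts that pass with OR > 1 is about 2.1.

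**Reading 2: group is tested as one 3-level factor** (likelihood ratio test, 2 df). Shares failing P < .1 in 200,000 simulated trials per row, at 79 and 88 per group:

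| Control / counseling / reminder | 3-level factor fails | Counseling dummy alone fails | Reminder dummy alone fails |
|---|---|---|---|
| 22 / 50 / 25% (protocol) | 1.7%, 0.9% | 1.7%, 1.0% | 86.4%, 86.2% |
| 22 / 35 / 25% (illustrative) | 48.9%, 45.1% | 43.1%, 38.9% | 86.5%, 86.2% |
| 22 / 30 / 25% (illustrative) | 73.8%, 72.1% | 68.7%, 66.3% | 86.6%, 86.2% |

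These figures cover the univariate screen only. Removal at the final selection step could add to them and is not sized here.

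**Ocular condition.** In the second dry run (Results), 14 of 38 children had naso-lacrimal duct obstruction and 7 had amblyopia. Table 1 puts both on 4-week schedules: 21/38 = 55%. Most of the other diagnoses reported there carry shorter intervals. The documents give no compliance rates by condition, so the gain from adjustment cannot be calculated.

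**The case against.** The strongest reply is that the trial's main comparison does not pass through this model. Outcomes and Compliance to Follow-up call for a comparison of proportions across groups, Sample Size is built on proportions with three comparisons, and Univariate Analysis gives odds ratios with confidence intervals before any selection. This stands. A reader might infer that the trial could end with no usable group comparison, and the documents do not support that.

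A second reply is that the list of independent variables covers one class, sociodemographic factors, and is not worded as exhaustive. The absence of study group from it therefore does not show that group is excluded, and the clause on variables of known importance could admit it. This stands in part. The clause names no variable, and it governs entry only, so significance can still remove a term from the final model.

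A third reply is that the 86% figure assumes dummies are screened one at a time, whereas Multivariate Analysis also speaks of overall significance by likelihood ratio test, which points to testing the factor whole. This also stands: 86% belongs to one reading, and it largely reflects low power for a hypothesised 3-point difference. On the other reading the risk is 1-2% at the protocol's rates, but that low risk depends on counseling reaching 50%.

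Finally, it is tempting to call visit gap the strongest prognostic factor the protocol names. The Introduction does not rank it. It mentions long gaps in passing as part of forgetting, beside lack of awareness, and cites distance and cost as major barriers in another study.

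**Conclusion.** The point holds for the adjusted analysis. The article states a full selection rule, so this is not a detail left to a statistical analysis plan, and nothing in the rule protects the group term. Crude group comparisons are unaffected.

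The adjusted reminder effect is the most exposed: about 86% of trials would screen it out if dummies are judged singly, and when it is retained in the right direction its median odds ratio is about 2.1 against a true 1.18. If group is judged as one factor, the risk is about 1-2% at 22/50/25%, about 45-49% if counseling reaches 35%, and about 72-74% if it reaches 30%.

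These figures rest on the 22% at-least-1-visit rate standing in for completion of all 3 visits, on 79 to 88 children per group, and on group having to pass the screen rather than being admitted as a variable of known importance. The 35% and 30% rates are illustrative. The lack of an assured place for condition or interval is a secondary matter of precision and of chance imbalance, and its size is unknown.

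**What to change.** Amend Multivariate Analysis to state that:
- the adjusted model has completion of all 3 visits as its outcome (the section now words the dependent variable as a before-after change and should be aligned with Outcomes);
- study group is always retained as a 3-level factor, with routine care as reference, whatever its P value;
- the covariates are a short list fixed in advance that includes ocular condition or its Table 1 visit interval;
- selection by P value is used only for the secondary analysis of sociodemographic factors.

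The change is to wording, at the price of a few degrees of freedom. Diagnosis is evidently recorded, since Results reports it for the dry run. The proforma is not shown, so whether the planned interval is its own field cannot be confirmed. For keratitis and ocular injury, where Table 1 makes the interval depend on severity, the interval would have to come from the schedule advised for the child.

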### Study Procedure

All participants will be enrolled in the study after fulfilling the inclusion criteria and administering informed consent. Recruitment will be conducted over a 6-month period. Participants will be assigned a unique code which will be a 6-digit number generated by using the last 3 digits of the patient’s medical record number and the last 3 digits of the parent’s or guardian’s mobile phone number. The participants will be entered into 3 groups, such that the first patient will be enrolled to the routine standard care group, the second to the counseling group, and the third to the group of SMS texts and phone call reminders. The same sequence will be followed for every participant until the required sample size has been attained. Before the actual start of the recruitment, 2 dry runs were conducted to understand the flow of the patients and logistics of the study.

After registration, the patient will be guided by the Outpatient Department (OPD) facilitator to the vision and refraction room and then to the consultant room. After ocular examination, treatment and follow-up advice, the consultant will paste a colored sticker on the patient’s file to indicate the potential study participant. There will be a separate and dedicated place for the pediatric ophthalmologist, assistant, and the counselor (Multimedia Appendix 1).

Patients with a colored sticker on their OPD file will be referred to the assistant room. The assistant will take the written consent from the children in an assent form (if 9 years or older) and from their parents or guardians in a consent form after explaining the study and group and selection to them (Multimedia Appendix 2 and 3).

A unique number will be allotted to the patient (generated through the medical record number and mobile phone number of the patient). The unique ID of the participants will be recorded in the proforma and on the examination file by the assistant. He will fill all the details in the proforma (Multimedia Appendix 4) and also enter the details in a Microsoft Excel sheet.

The patients assigned to counseling will be sent to the counselor. The counselor will conduct a counseling session based on the ocular condition and follow-up plan. Counseling will be done as per the prescribed counseling protocol. After counseling, the counselor will provide the information leaflets, and the patient will be asked to visit the optical dispenser or pharmacist.

For patients assigned to the SMS text and phone call reminders or control groups, the necessary details will be filled in the proforma and Excel sheet before they are discharged by the assistant.

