## Methods

### Study Design and Setting

This public health intervention study will be conducted at Hiralal Santudevi Pradhan Institute of Ophthalmic Sciences which includes 13 satellite clinics and 1 base hospital (Bharatpur Eye Hospital [BEH]). The study participants will be enrolled only from the pediatric department of BEH, a centrally located tertiary eye hospital in the Chitwan district of Nepal. All pediatric patients 0 to 16 years of age meeting the inclusion criteria will form the study population. In the pediatric department of BEH, children aged 0 to 16 years are being examined as per the hospital policy.

The inclusion criteria are all pediatric patients 0 to 16 years of age advised for at least 3 follow-up visits within a 6-month period at BEH, parents or guardians of children who own a mobile phone or have daily access to a phone and are able to use the SMS text feature on these phones, and parents willing to enroll their children in the study.

The exclusion criteria are children who require fewer than 3 follow-up visits, children with ocular conditions requiring daily follow-up visits (because it is not feasible to send the reminder phone call and SMS text for daily follow-up), children who have already been treated and are under regular follow-up, children with ocular conditions requiring follow-up beyond 6 months, parents or guardians of the children who are not willing to participate in the study, and those who have been called but do not answer after 3 attempts

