#### SMS Text and Phone Call Reminder Group

In this group, after the children have been examined and a treatment plan and the follow-up have schedule been advised, they will be discharged from the department. They will receive an SMS text 3 days prior to and a phone call 1 day prior to their scheduled follow-up visits. Text messages will be sent until it is confirmed that the sent message has been received. In the case of message delivery failure, it will be sent again 3 more times to ensure successful delivery. If the SMS text is not delivered after 3 attempts, then a message will be sent to the next phone number (if available) as recorded in the proforma during the interview. A phone call will be deemed to be completed once it is received by the respondent; calls will be repeated at least 3 times if the phone is not answered in the first instance. If the call is not answered even after 3 attempts, the participant will be excluded from the study.

The assistant (DA) will be responsible for making the reminder SMS and calls, making the records, and tracking the follow-up patients. The standard text and the call format have been developed in the local language (Nepali).

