### Record Maintenance

Records of the participants from the first visit to all the follow-up visits will be maintained in the department by the assistant. The details will be entered for each participant as per the proforma. If both parents accompany the child, only the mother’s detail will be included. However, when both parents accompany the child but only the father has access to a mobile phone, his details will be recorded.

The record of the patients will be kept even if they come for follow-up beyond the set window period (2 days); however, in this case, they will not be considered compliant to follow-up.

The assistant will also assign the patients to a group (regardless of whether they receive an intervention) as per the study procedure. A follow-up recording file (3 in number, 1 each for routine standard care, counseling, and reminders through SMS texts and phone calls) will be maintained. These follow-up details will also be entered in the Excel sheet on the same day as a backup in case the paper records are lost or destroyed. The entry of all the details from the proforma will be entered and stored in an Excel sheet by the assistant. The status of record maintenance will be regularly monitored by the ophthalmic officer (BP). The assistant will also be responsible for tracking the follow-up visits and updating the schedule for executing the reminder SMS texts and phone calls (Multimedia Appendix 5).

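### Allocation follows a fixed three-arm rotation, and the assistant who takes consent also assigns the group, so the next arm is known before each family agrees to join

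*Protocol article*

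**What the plan says.** The Protocol article, Study Procedure, sets the order of assignment: "the first patient will be enrolled to the routine standard care group, the second to the counseling group, and the third" to the reminder group. It continues: "The same sequence will be followed for every participant until the required sample size has been attained".

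The same section describes enrolment. After the examination, "the consultant will paste a colored sticker on the patient’s file to indicate the potential study participant", and flagged patients go to the assistant's room. On consent it says: "The assistant will take the written consent from the children in an assent form (if 9 years or older"), and from parents or guardians on a consent form, "after explaining the study and group and selection to them".

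Record Maintenance names the person who allocates: "The assistant will also assign the patients to a group (regardless of whether they receive an intervention) as per the study procedure". It also has the assistant keep a separate follow-up file for each group. The section on the SMS and phone reminder group adds that the assistant "will be responsible for making the reminder SMS and calls, making the records, and tracking the follow-up patients".

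Eligibility under Study Design and Setting includes "parents willing to enroll their children in the study", so entry depends in part on a conversation that the assistant conducts.

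**The concern.** A rotation has no random element. Anyone who knows the last assignment knows the next one, and here that person is also seeking agreement to take part. How firmly a hesitant family is encouraged can then vary, even unintentionally, with the arm they would enter. The rotation counts enrolled participants, so on its plain reading a refusal leaves the slot to the next family.

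This matters more than usual because the outcome is attendance. A family's motivation to return drives that outcome, and staff can partly judge it at the first visit. The primary objectives ask whether counseling and reminders change follow-up, which is a causal question. The Discussion says that any intervention found effective will become hospital policy. If the arms differ in motivation at entry, the comparison mixes that difference with the effect of the intervention.

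**Working it through.** **1. Is the rule really deterministic?** Study Procedure fixes the order and repeats it to the full sample size. The dry run in Results agrees: 38 = 3 × 12 + 2, so a strict rotation gives 13, 13 and 12 in the order standard care, counseling, reminders. Those are the reported numbers. Balanced random blocks could give the same split, so this is consistent with the rule and does not prove how it was applied.

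**2. How predictable is the next arm?** Take a person who knows all past assignments and guesses the most likely next arm.

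| Method | Next assignments guessed correctly |
|---|---|
| Fixed rotation | 264/264 = 100% |
| Simple 1:1:1 randomization, concealed | 1/3 = 33% |
| Permuted blocks of 3, unconcealed | (1/3 + 1/2 + 1)/3 = 61% |
| Permuted blocks of 6, 9, 12, unconcealed (simulated, 4,000 runs) | about 56%, 53%, 51% |

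A random list alone is therefore not enough. Without concealment, more than half of the assignments could still be guessed.

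**3. Who holds this knowledge, and when?** The assistant takes consent (Study Procedure), assigns the group and keeps the three group files (Record Maintenance). The next arm is thus known to the person seeking consent before the form is signed. The consultant flags patients one step earlier and could learn the rotation too.

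**4. Can the planned model repair it?** Independent Variables lists gender, age, ethnicity, education, occupation, the attendant's relationship to the child, distance and travel cost. Motivation to return is not measured. The logistic model under Multivariate Analysis can adjust only for measured factors.

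**5. What can still be changed?** As of September 2021, 154 of 264 were enrolled (58.3%). The remainder is 264 − 154 = 110, or 110/264 = 42%, about 37 per arm.

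**6. What could the concealed part show alone?** Use the plan's 50% against 25%, a two-sided level of .05/3 and n = 37 per arm. The pooled normal formula is z = (|p1 − p2|√n − z_α√(2p̄q̄)) / √(p1q1 + p2q2).

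With p̄ = 0.375 and z_α = 2.394: (0.25 × 6.083 − 2.394 × 0.685)/0.661 = −0.18. Power is about 43%. With 36 per arm it is about 42%. With 10% loss (33 per arm) it is about 38%.

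**The case against.** **The study does not call itself randomized.** It is presented as a public health intervention study and states the rotation openly. This stands: the point is a weakness in a declared design, and a reader who infers that the article contradicts itself goes too far.

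**The family may not learn its own group before deciding.** The wording "after explaining the study and group and selection to them" can mean the three groups and how families are chosen, as any consent discussion requires. The consent form is not shown. This also stands: that the family's own decision depends on the arm is a possible inference, but it holds only if that family's own group is disclosed beforehand. Foreknowledge by staff remains on either reading.

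**Discretion is limited.** A consultant flags patients, inclusion covers all who meet the criteria, and no text lets the assistant choose the order of approach. That narrows the route for bias to encouragement at consent, and to flagging if the consultant learns the rotation. It does not close it, because parental willingness is an entry criterion.

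**Monitoring exists.** Checks by the ophthalmic officer, comparison with the proformas and weekly monitoring bear on the accuracy of records, not on concealment. Likewise, the assistant's work in sending reminders and tracking visits raises questions of delivery and ascertainment, which are separate from selection at enrolment.

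**The size cannot be taken from the 22% rate.** A reader might move a few likely attenders between arms of 88 (0.22 × 88 = 19.36 attenders each) and read off a false difference. The documents do not support this. The 22% is attendance at one or more visits, whereas the primary outcome is completion of all 3, with a 2-day window for compliance. In the second dry run 7 of 38 attended, and none went beyond the first visit. At an assumed completion rate of 5%, an arm would hold only 0.05 × 88 = 4.4 completers.

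**Conclusion.** The concern holds as a design weakness. Every assignment is known in advance to the person who takes consent, no concealment is described, and the planned adjustment cannot remove selection on motivation. The firm figure is the predictability: 100%, against 33% under concealed simple randomization.

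The amount of bias in the follow-up rates is unknown. A reader might infer that the groups already differ, but nothing in the documents shows this. The conclusion assumes only that staff follow the stated rotation and that enrolment depends partly on the consent discussion, both of which the article says.

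**What to change.** 1. **For any participants not yet enrolled** (110 as of September 2021; the current number is not known), replace the rotation with a computer-generated list in randomly varying permuted blocks. Someone outside enrolment should prepare it. Hold the assignments in sequentially numbered opaque sealed envelopes, each opened only after consent, and assent where it applies, is signed.
2. **At consent**, still tell families about the three-group design, but do not tell them their own group until they have agreed.
3. **Log families approached and refusing** by the arm that was next, including earlier families where records allow.
4. **In all reports**, describe participants already enrolled as alternately allocated without concealment.
5. **As a prespecified sensitivity analysis**, report treatment effects separately by allocation method, with an arm-by-period contrast. A period main effect alone is not enough: it absorbs an overall difference between periods but leaves arm-specific selection among the 154 in place.

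The cost is a short amendment, a list and a set of envelopes. The downside is two allocation methods in one trial, with power of roughly 38% to 43% in the concealed part alone, so the separate analysis can only be supportive. If enrolment has closed, item 1 no longer applies. The description, the refusal counts where logged and a plain statement of the limitation remain possible.
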